### Outcome measures

2.7

The related indexes of the 2 groups will be detected before and after radiotherapy and chemotherapy, and the relevant data will be recorded.

Energy intake: the dietitian uses the 24 hours retrospective method to conduct a dietary survey once a week, including the type and quantity of diet. The daily energy intake is calculated according to the Chinese Food composition Table 2002, and the body mass is measured once a week.

Hematological determination: the levels of leukocyte, hemoglobin, platelet, total protein, albumin, prealbumin, and transferrin were detected after fasting venous blood collection.

Quality of life assessment: SF-36 score (the MOS item short from health survey).

Adverse reactions: The evaluation of adverse reactions refers to the Evaluation criteria of Common adverse events of the National Cancer Institute of the United States.^[13]^

### Data collection and management

2.8

Nutrition intervention will run through the whole process of radiotherapy and chemotherapy. According to the outcome indicators, the data before radiotherapy and chemotherapy, every two weeks after the beginning of radiotherapy and chemotherapy, and after radiotherapy and chemotherapy are collected. All data will be collected by an assistant, and recorded in detail in the predesigned table. All the research data will be stored in a separate window, and only the researchers of this research group can access the relevant research data.

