### Sample size calculation

2.5

This study is a pilot clinical trial. The calculation of the sample size is based on the withdrawal rate of 20% in the clinical study, taking *α* *=* *0.025, power* *=* *90%,* referring to the previous literature.^[9]^ According to the albumin level after radiotherapy, the average score of the test group is 33.3, and the standard deviation is 2.68. The average of the control group is 28.5, and the standard deviation is 3.83. It will be calculated that the minimum number of patients would be included in each group is 25.

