### Statistical analysis

2.9

The data will be statistically analyzed by SPSS 16.0. The counting data will be expressed by rate, $\chi^{2}$ test will be used, and the measurement data will be expressed by $\bar{x}\pm s$. A *t* test will be used for comparison between groups. The difference is statistically significant when *P* < .05.

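### The t test named for continuous outcomes uses neither the baseline value nor the two-weekly data of patients who withdraw; a baseline-adjusted mixed model would use both

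*Protocol article*

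**What the plan says.** The relevant statements are all in the protocol article.

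- **Section 2.8, Data collection and management.** Data are taken before treatment, and then "every two weeks after the beginning of radiotherapy and chemotherapy, and after radiotherapy and chemotherapy are collected".
- **Section 2.7, Outcome measures.** The opening sentence gives two occasions only: "The related indexes of the 2 groups will be detected before and after radiotherapy and chemotherapy". The energy-intake paragraph then has the dietitian "conduct a dietary survey once a week", and adds that "the body mass is measured once a week".
- **Section 2.5, Sample size calculation.** The size is "based on the withdrawal rate of 20% in the clinical study" and on albumin after radiotherapy: mean 33.3 (SD 2.68) in the test group and 28.5 (SD 3.83) in the control group. The stated minimum is 25 per group.
- **Section 2.9, Statistical analysis.** For measurement data a t "test will be used for comparison between groups", with significance at P < .05. For categorical outcomes, "The counting data will be expressed by rate" and a chi-square test applies. Section 2.9 names no time point, baseline adjustment or repeated-measures method.

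**The concern.** The design yields a series of values per patient and expects one patient in five to leave. The one method named for continuous outcomes compares two sets of single values. Used on end-of-treatment values, it takes nothing from baseline and nothing from the interim visits of patients with no final value.

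Two things follow. First, precision is given away, because baseline albumin or body mass usually predicts the later value. Second, if patients whose nutrition is already failing are more likely to withdraw, those with a final value are a selected group. The selection can differ by arm, since only one arm receives the supplement. Section 3 says that malnutrition affects the course of treatment and that ordinary diets fall short of energy targets, so such a link is plausible. The article does not assert it and gives no withdrawal rates by arm.

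The timing is also loose. Section 2.5 refers to albumin after radiotherapy, section 2.7 to before and after combined treatment, and section 2.8 adds two-weekly collection. The visit to which the t test belongs is therefore not fixed.

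**Working it through.** **1. The plan's own figures.** The planned difference is 33.3 − 28.5 = 4.8. The pooled SD is √((2.68² + 3.83²)/2) = 3.305. With n = 2(z_α + z_β)²σ²/δ² and 90% power:

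- one-sided 0.025: 2 × (1.960 + 1.282)² × 3.305² / 4.8² ≈ 10 per arm, or 10/0.8 → 13 with withdrawal;
- two-sided 0.025: 12 per arm, or 12/0.8 = 15 with withdrawal.

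The stated 25 is not reproduced with the pooled SD. That is a separate matter. Here I take 25 as given, so 20% withdrawal leaves 25 × 0.8 = 20 per arm with a final value.

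**2. Power.** With 20 per arm the standard error of the difference is 3.305 × √(2/20) = 1.045. Power for 4.8 is about 99% (99.6% at one-sided 0.025, 99.1% at two-sided 0.025). Lost power is not the problem.

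**3. Precision from baseline.** Adjusting for a baseline value with correlation r to the final value multiplies the variance by about 1 − r². The article gives no r, so a range is assumed:

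| r | 1 − r² | SE = 1.045 × √(1 − r²) |
|---|---|---|
| 0.3 | 0.91 | 1.00 |
| 0.5 | 0.75 | 0.91 |
| 0.7 | 0.51 | 0.75 |

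**4. Bias when withdrawal depends on an earlier value.** This was simulated with large samples.

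- From section 2.5: final means, SDs and 20% overall withdrawal.
- Assumed: earlier-visit means of 31 (control) and 34.5 (ONS), with the same SDs; correlation r between the two visits; log-odds of withdrawal falling by a fixed slope per unit of earlier albumin, with the intercept set to give 20% overall. The split of withdrawal by arm follows from these assumptions.

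The true difference is 4.8 throughout. The last column is what a t test on patients with a final value would estimate.

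| Slope | r | Withdrawal, control / ONS | Difference seen |
|---|---|---|---|
| −0.4 | 0.7 | 30% / 10% | 4.1 |
| −0.4 | 0.5 | 30% / 10% | 4.3 |
| −0.2 | 0.7 | 26% / 14% | 4.5 |
| −0.2 | 0.5 | 26% / 14% | 4.6 |
| −0.1 | 0.7 | 23% / 17% | 4.7 |
| −0.1 | 0.5 | 23% / 17% | 4.7 |

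The shortfall runs from about 3% to (4.8 − 4.1)/4.8 ≈ 15%. In the first row, regressing the final value on the earlier one within each arm and averaging over everyone randomised gives 4.8 again. A mixed model draws on the same information.

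**5. Effect on the conclusion.** Even at 4.1 with 20 per arm, power is about 97% at two-sided .05. In these scenarios the size of the estimate suffers, not the verdict on albumin.

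**The case against.** The strongest reply is that a two-group t test on one end-of-treatment value is a legitimate analysis of a randomised comparison. The abstract and section 2.7 both speak of before and after treatment, and section 2.5 is sized on a single post-treatment value. The trial calls itself a pilot, and a condensed article may leave the analysis set and missing-data handling to a fuller plan. Much of this stands. The absence of those details is not the point here. The point is the method that section 2.9 positively names.

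A reader might infer three stronger things, and the article supports none of them.

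- **That only completers will be analysed.** Section 2.9 does not say so. A t test could be run on change from baseline, or after imputation.
- **That each visit will be tested, raising the false-positive rate.** Nothing states this. If it were done at .05 with 3 or 4 visits (an assumed number), the chance of at least one false positive per outcome would be about 10% to 17% for serial correlation 0.8 to 0.5. That figure belongs to a procedure the plan does not describe.
- **That the t test is the only analysis.** The chi-square test is also named, so the statement holds for continuous outcomes only.

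The bias figures are likewise illustrations. Slope, correlation, earlier means and the resulting split by arm are all assumed, and 15% is the largest of six settings. The timing differences are partly wording: section 2.8 ties collection to the outcome indicators, and the albumin phrase in section 2.5 introduces values from the literature.

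What remains is that a t test on the single final value still sets aside baseline and the earlier values of patients who leave.

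**Conclusion.** The point holds in a limited form. For continuous outcomes the stated test fits poorly with two-weekly collection and 20% expected withdrawal. Baseline is left unused, which costs precision: the variance could be 9% to 49% lower for an assumed correlation of 0.3 to 0.7. If withdrawal depends on earlier nutritional status, the estimate can be biased. Under the assumed models a true albumin difference of 4.8 appears as about 4.1 to 4.7. The direction in practice is unknown: the reverse pattern of withdrawal would push it the other way, and that has not been sized. Neither power nor the false-positive rate of a single end-of-treatment test is in question. The measurement times in sections 2.5, 2.7 and 2.8 do differ and should agree. This is a cheap improvement, not a flaw that invalidates the trial.

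**What to change.** - In section 2.9, replace the t test for repeatedly measured outcomes with a linear mixed model in all randomised patients, analysed as randomised. Include arm, visit, arm by visit and the baseline value.
- Name one end-of-treatment visit and take the arm difference there as the test. Report the other visits descriptively.
- Make sections 2.5, 2.7 and 2.8 state the same visit schedule for each outcome and the same final visit.
- State the model's limits. It protects against withdrawal that depends on recorded values, not on unrecorded ones. A patient with no value after baseline adds nothing to the estimate, so report how many there are in each arm.

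The cost is a change of wording and slightly more programming. With about 25 patients per arm an unstructured covariance may not fit reliably, so a simple structure may be needed and should be named in advance. No new data or patients are required.

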### Statistical analysis

2.9

The data will be statistically analyzed by SPSS 16.0. The counting data will be expressed by rate, $\chi^{2}$ test will be used, and the measurement data will be expressed by $\bar{x}\pm s$. A *t* test will be used for comparison between groups. The difference is statistically significant when *P* < .05.

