**Methods::**

This is a prospective randomized controlled trial to study the effects of oral nutritional supplement therapy on nutritional status and quality of life in patients with esophageal cancer undergoing radiotherapy and chemotherapy. This study is approved by the Clinical Research Society of our hospital. Patients will be randomly divided into ONS group and traditional diet group. The nutritional status, quality of life score and adverse reactions will be observed before and after radiotherapy and chemotherapy. The data will be analyzed by SPSS 16.0.

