### Randomization and blinding

2.4

This study will be randomized into groups without any stratification. Through simple randomization, the patients in the study will be divided into the observation group and the control group according to the 1:1 ratio. Due to the limitation of the intervention in this study, this study cannot achieve strict double-blindness. We will ensure that the study designer, allocators, data analysts, intervention supervisors, and some researchers are blind to personnel allocation.

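### Section 2.9 fixes a plain between-group t test with no baseline term; the test is valid, but it discards precision that the pre-treatment values already collected would give

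*Protocol article*

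**What the plan says.** Section 2.9 (Statistical analysis) assigns rates to a chi-square test and means to a t test. Of the latter it says only that it "test will be used for comparison between groups", with significance at P < .05. No baseline covariate, change score or repeated-measures model is named.

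The baseline is nevertheless collected. Section 2.7 (Outcome measures) states: "The related indexes of the 2 groups will be detected before and after radiotherapy and chemotherapy". Section 2.8 (Data collection and management) lists "the data before radiotherapy and chemotherapy, every two weeks after the beginning of radiotherapy and chemotherapy, and after radiotherapy and chemotherapy are collected". The abstract likewise has nutritional status and quality of life observed at both times.

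The design does not balance starting values. Section 2.4 says "This study will be randomized into groups without any stratification" and describes simple 1:1 allocation.

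Section 2.5 plans 25 patients per group with 20% withdrawal, from post-treatment albumin means of 33.3 and 28.5 (SDs 2.68 and 3.83). Section 2.6 starts the nutrition programme 3 days before radiotherapy and chemotherapy.

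**The concern.** Starting nutritional status is likely to predict nutritional status at the end of treatment. A comparison of final values that ignores it leaves that predictable variation in the error term, so confidence intervals are wider than they need be. It also leaves any chance difference in starting values in the estimate, where it can exaggerate or mask an effect. With about 20 evaluable patients per arm and no stratification, such differences are not rare. The remedy uses data that the trial will hold anyway.

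**Working it through.** **Inputs from the protocol.** Planned albumin difference 33.3 − 28.5 = 4.8; SDs 2.68 and 3.83; 25 per group; 20% withdrawal (section 2.5). P < .05 is taken as two-sided (section 2.9).

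**Assumptions.** The documents do not give the baseline-to-final correlation r, so I use 0.3, 0.5 and 0.7. Baseline SD is assumed equal to final SD.

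**The plan's own figure.** The root mean square SD is √((2.68² + 3.83²)/2) = 3.305. At 90% power the need is 10 to 12 per group by the normal formula and 12 to 14 by the t-based one, or 13 to 18 after dividing by 0.8. The stated 25 is not reproduced this way. That is a separate matter; here 25 is taken as given, leaving 25 × 0.8 = 20 evaluable per arm.

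**Precision.** The SE of the unadjusted difference is 3.305 × √(2/20) = 1.05. ANCOVA multiplies the variance by about 1 − r². A t test on change multiplies it by 2(1 − r). Power is shown for an illustrative albumin difference of 2.4, half the planned one; unadjusted power for it is 0.632.

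| r | ANCOVA variance factor | SE | Equivalent n per arm, 20/(1 − r²) | ANCOVA power at 2.4 | Change-score factor | Change-score power at 2.4 |
|---|---|---|---|---|---|---|
| 0.3 | 0.91 | 1.00 | 22.0 | 0.673 | 1.40 | 0.492 |
| 0.5 | 0.75 | 0.91 | 26.7 | 0.755 | 1.00 | 0.632 |
| 0.7 | 0.51 | 0.75 | 39.2 | 0.895 | 0.60 | 0.842 |

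ANCOVA costs one residual degree of freedom (40 − 3 = 37 instead of 40 − 2 = 38).

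**Planned effect.** At 4.8, the unadjusted z is 4.8/1.045 = 4.59, and 4.59 − 1.96 = 2.63, giving power 0.996.

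**Chance imbalance.** In SD units, the baseline difference has SE √(2/20) = 0.316.
- P(above 0.3 SD): 0.3/0.316 = 0.95, two-sided probability 0.34.
- P(above 0.5 SD): 0.5/0.316 = 1.58, two-sided probability 0.11.
- In albumin units, the 95% range is ±1.96 × 1.045 = ±2.05, about 43% of 4.8. The unadjusted final-value estimate carries r times the baseline difference: at that limit, 0.6, 1.0 or 1.4 units for r = 0.3, 0.5 or 0.7.

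**Conditional type I error of the final-value t test.** Given a baseline difference of 0.5 SD and no treatment effect, the final difference has mean 0.5r and SD 0.316√(1 − r²). The test rejects beyond 1.96 × 0.316 = 0.620.
- r = 0.5: mean 0.25, SD 0.274; (0.620 − 0.25)/0.274 = 1.35; with the small lower tail, 8.9%.
- r = 0.7: mean 0.35, SD 0.226; (0.620 − 0.35)/0.226 = 1.20; 11.6%.
- At 0.3 SD, simulation with 20 per arm gives about 4.6% (r = 0.5) and 3.6% (r = 0.7), both below nominal.

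**The case against.** **The t test is valid.** This stands. Over all randomisations it is unbiased and keeps its 5% level. A reader might infer from the conditional figures that the planned test has inflated type I error; the documents do not support that. A reader might also join the 34% chance of an imbalance above 0.3 SD to the 9% to 12% error rate. Those figures belong to different imbalances: the error rate is for 0.5 SD, exceeded with about 11% probability, and at 0.3 SD the conditional level is below 5%.

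**The t test may be on change.** Section 2.9 does not say. Section 2.5 plans on albumin after radiotherapy, which makes final values the likelier reading without settling it. A change score does use the baseline, so it cannot be said flatly that the baseline is ignored. But a change-score test gains nothing at r = 0.5, is worse below that, over-corrects imbalance, and has a larger variance than ANCOVA at each r shown.

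**Albumin is already well powered.** This stands at the planned 4.8. It does not cover smaller albumin effects or the outcomes for which no planning figures are given.

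**The correlation is assumed.** This also stands. It may be low for 24-hour recall intake or for blood counts during chemotherapy, where the gain could be nearer 9% than 49%.

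**This is a condensed article of a self-described pilot.** A fuller analysis plan may add adjustment. But section 2.9 does more than stay silent: it names the test, and an ANCOVA written later would depart from it.

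**Conclusion.** The point holds as a matter of efficiency and of conditional bias, not of validity. For the measurement outcomes, the stated t test is at least as imprecise as ANCOVA on either reading, apart from the one degree of freedom. The variance reduction forgone is about 9%, 25% or 49% at an assumed r of 0.3, 0.5 or 0.7.

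It matters most for SF-36, body mass, energy intake and the blood values other than albumin, and for albumin effects below the planned one. It does not show that the trial is underpowered for albumin as planned. Nor does it reach every outcome: adverse reactions are count data for the chi-square test. The change is worth making before analysis, but the plan is not unsound without it.

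**What to change.** In section 2.9, replace the t test as the main analysis of each measurement outcome by ANCOVA: final value as response, arm as factor, and the baseline of the same variable as covariate. Report the adjusted mean difference with its 95% CI, and keep the unadjusted t test as supportive.

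Define that baseline as a measurement taken before the nutrition programme starts. Section 2.8 asks only for a value before radiotherapy and chemotherapy, while section 2.6 starts the programme 3 days before them. A value taken in that interval could already reflect the intervention, most obviously for energy intake. Leave count data with the chi-square test.

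The cost is a sentence or two of text and attention to the date of the baseline measurement. No additional patients, visits or variables are needed.

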## Discussion

3

Nutritional support has become an important part of tumor treatment. Ideal nutritional support should be based on the accurate assessment of the nutritional status of patients. ONS is a kind of nutrition supplement for special medical purpose, which can increase the intake of energy and nutrients. It is economical, convenient and easy to be accepted by patients.^[14]^ ONS is the preferred nutritional route recommended by both Chinese and European guidelines for tumor patients.^[15,16]^ Oral nutritional supplement plays an irreplaceable role in improving the tolerance of tumor patients, improving the nutritional status of tumor patients during radiotherapy, and even prolonging their life cycle.

Radiation esophagitis, dysphagia, and pain often occur in patients with esophageal cancer after radiotherapy, and malnutrition affects the course of treatment.^[17]^ Studies have shown that malnutrition is an independent risk factor for poor prognosis in patients with esophageal cancer.^[18]^ During radiotherapy and chemotherapy, many patients with esophageal cancer have difficulties in eating solid food, but an ordinary half-stream diet and liquid diet cannot meet their target energy requirements.^[3]^ Due to the hindrance of protein synthesis in the liver and abnormal protein metabolism, tumor patients are prone to decrease in varying degrees of protein (including albumin, prealbumin, transferrin).^[19]^

Although studies have confirmed that ONS can supplement the lack of energy and protein in patients with esophageal cancer, maintain and increase the weight of patients, improve nutritional status, and improve the quality of life,^[9]^ there is still a lack of strict RCTs to support this conclusion. In this study, a strict randomized controlled method will be used to evaluate the effect of oral nutritional supplement therapy on nutritional status and quality of life in patients with esophageal cancer undergoing radiotherapy and chemotherapy.

This study also has the following limitations: due to the factors of intervention, researchers and patients cannot strictly achieve double-blind, there may be a certain bias; there is a regional population included in this study, which may have a certain impact on the results.
